## Abstract

**Background:**

Fear of cancer recurrence (FCR) is one of the most frequently cited problems by cancer survivors. More than one third report high FCR, which is a clinical concern due to its association with negative health outcomes. The aim of the current study is to evaluate the efficacy of cognitive behaviour therapy (CBT) in reducing FCR in high fearful cancer survivors.

**Methods/design:**

The SWORD-study has a randomised controlled design with two arms. A sample of 104 high fearful cancer survivors (breast, prostate or colorectal cancer) will be recruited from local hospitals. Cancer survivors will be randomised to receive CBT (intervention condition) or treatment as usual (control condition). For those in the intervention condition, the therapy will be individually delivered in a combination of 5 face-to-face therapy sessions and 3 online or telephone sessions by a trained therapist. Furthermore, these survivors will have access to a supportive website (or workbook) throughout the therapy. Survivors in the control condition will not receive the intervention and will not have access to the website. The primary outcome will be severity of fear of recurrence (Cancer Worry Scale). Quality of life (EORTC Quality of Life Questionnaire Core 30) and general psychological wellbeing will be assessed as secondary outcomes. Assessments will take place at baseline (before random assignment), at 3, 9 and 15 months after the baseline assessment. The study has been approved by an ethical review board.

**Discussion:**

If the intervention proves to be effective an evidence-based therapy to manage high FCR will become available for use in clinical practice.

**Electronic supplementary material:**

The online version of this article (doi:10.1186/s40359-015-0068-1) contains supplementary material, which is available to authorized users.

## Background

The number of people diagnosed with cancer is steadily increasing while medical advancements have significantly decreased cancer mortality rates. In the period beyond diagnosis and active treatment cancer survivors are faced with several emotional challenges. Handling fear of cancer recurrence (FCR) is one of the most prominent ones (Crist & Grunfeld 2012).

FCR is defined as ‘the fear or worry that the disease will return or progress in the same organ or in another part of the body’ (Vickberg 2003). FCR is a universal concern that manifests itself on a continuum, with mild uncertainty and worry on one end to severe FCR on the other end. A certain level of FCR is therefore considered normal and may even be functional; it motivates appropriate self-protective responses (e.g. staying alert for signs of a potential recurrence). However, high FCR can detrimentally affect a survivors’ emotional wellbeing (Simard et al. 2013) and may persist for years after completion of medical treatment (Savard & Ivers 2013; Deimling et al. 2006).

Moderate to high FCR is present in about 30 to 70% of cancer survivors (Savard & Ivers 2013; Custers et al. 2014; Thewes et al. 2012; Simard & Savard 2007). High FCR represents a form of distress related to the illness and aspects of treatment e.g. the cancer itself, follow-up care or periodic examinations. It is also related to psychosocial concerns such as worries about the future, disability or death (Mehnert et al. 2009). FCR is in the top five of greatest concerns for cancer survivors and has consistently been identified as one of the most cited unmet needs (Simard et al. 2013; Armes et al. 2009). Even though the problem is frequently encountered in clinical practice, no clear consensus exists on the best management strategies due to the scarcity of evidence-based therapies. This makes FCR a challenging problem for many survivors and health care providers (Thewes et al. 2014).

### Interventions for FCR

A more detailed description of intervention studies that have specifically addressed FCR (or related constructs) can be found in Additional file 1: Appendix A. Only one trial specified FCR as primary outcome of interest. Lebel et al., (2014) published a feasibility and preliminary outcome study of a single-arm 6-week cognitive existential group intervention to address moderate to high FCR in breast- and gynaecological cancer survivors. A decrease in FCR was found immediately following completion of the therapy and this effect was sustained at the 3-month follow-up. In 71% of the cancer survivors FCR could be classified as reliably improved and none of the cancer survivors showed deterioration (Lebel et al. 2014).

A construct that shares some defining features with FCR is fear of progression (FoP), the fear that the disease will further spread or progress in the body. A trial by Herschbach et al. (Herschbach et al. 2010) compared the effect of two four-session group interventions (cognitive behaviour therapy vs. supportive-experiential group therapy) and usual care on reducing dysfunctional FoP (Herschbach et al. 2010). Both interventions were carried out during cancer rehabilitation. FoP decreased significantly over time (up to 12-month follow-up) in both intervention groups in contrast to the control group. Those with metastatic disease or a recurrence (21%) benefitted most from the interventions (Lebel et al. 2014). A secondary analysis of this data by Sabariego et al., (2011) showed superior cost-effectiveness of group CBT over supportive-experiential group therapy for patients with high FoP (Sabariego et al. 2011).

Four intervention studies to improve generic emotional outcomes in breast cancer survivors addressed FCR as secondary measure (see Additional file 1: Appendix B). Two studies by Lengacher et al. 2009, 2011 investigated short-term effects of group mindfulness-based stress reduction (MBSR) on psychological status in breast cancer survivors. In the first study, a randomised controlled trial (RCT), breast cancer survivors participating in a 6-week MBSR programme reported a significant reduction in FCR over time compared to breast cancer survivors on a waitlist control group Lengacher et al. 2009 A second study by Lengacher et al., (2011) found significant improvement in FCR after completion of an 8-week MBSR programme (Lengacher et al. 2011). Both studies have only assessed short-term effects of the intervention and no information on long-term efficacy is available (Lengacher et al. 2009; Lengacher et al. 2011). The third study, a non-randomised trial, reported a significant decline in levels of FCR (cancer worry) following a 12-week emotion regulation group intervention targeted at anxiety and distress in breast cancer survivors. Yet, no long-term beneficial effects were found at 6-month or 12-month follow-up (Cameron et al. 2007). Finally, a brief self-guided nurse delivered uncertainty management intervention found no significant differences between the intervention and control group (Mishel et al. 2005). We are aware of two separate intervention trials for FCR currently in progress: Conquer Fear (Butow et al. 2013) and the AFTER-intervention (Humphris & Ozakinci 2008). Results of these studies have not yet been published.

To summarize, published intervention studies provide promising results in terms of beneficial effects of psychological interventions for FCR and related constructs. However, these studies had some limitations. While literature shows that moderate to high FCR is a universal problem in cancer survivors interventions have almost solely focused on survivors with breast- or gynaecological cancer (Herschbach et al. 2010; Lengacher et al. 2009; Lengacher et al. 2011; Mishel et al. 2005). Furthermore, information on treatment efficacy for long-term cancer survivors is limited because FCR was mainly addressed during the first year after diagnosis (Herschbach et al. 2010; Lengacher et al. 2009; Lengacher et al. 2011). Therefore, it is hard to generalise findings of efficacy and feasibility beyond women’s cancers to other cancer types, to men and to long-term cancer survivors. Only two studies mention screening for high FCR as part of their standard eligibility procedure (Lebel et al. 2014; Herschbach et al. 2010). By screening for high (dysfunctional) FCR, it is possible to identify those with the highest care need and to select those who might benefit most from the intervention. The SWORD-study was developed to address above mentioned limitations.

### Current study

This paper describes the development of the intervention and study protocol for the SWORD-study (SWORD is the acronym for Survivors’ Worries of Recurrent Disease). In this study an intervention known as “Beyond Fear” will be evaluated with regard to its efficacy in managing high FCR among breast, colorectal and prostate cancer survivors. In an RCT both the short-term and long-term effects of individual CBT for FCR will be investigated.

Our intervention expands on the theoretical formulation of FCR as a multidimensional construct proposed by Lee-Jones (1997; Lee-Jones et al. 1997). We updated this original formulation with recent research findings and clinical experience. According to our framework as shown in Figure 1, FCR is a distressing emotion maintained by dysfunctional cognitive thinking patterns such as recurring unhelpful thoughts, negative (illness) beliefs, intrusive images or persistent rumination. These thinking patterns cause a person to interpret certain events or internal stimuli as potentially threatening or harmful to one’s physical health and wellbeing, thereby triggering FCR. Consequently, behavioural strategies that are intended to reduce the fear, such as avoidance, excessive self-monitoring or safety-seeking behaviours, maintain FCR by preventing change in cognitive appraisal and/or by providing further exposure to triggers of FCR. While these behaviours may provide short-term alleviation of fear, they may actually maintain the fear on the long run (Lee-Jones et al. 1997; Leventhal et al. 1980). CBT targets high FCR by changing dysfunctional thinking patterns and maladaptive behaviours as specified in this model.

**Figure 1 Fig1:**
[figure not shown]
Theoretical model fear of cancer recurrence.

### Aims

The primary aim of the SWORD-study is to evaluate the efficacy of a combination of online and face-to face cognitive behaviour therapy (blended CBT) in reducing the impact of FCR in breast, colorectal and prostate cancer survivors. The aim is not to remove all FCR, but rather to reduce its severity in order to improve quality of life.

## Methods/design

The SWORD-study design and intervention are described conform the CONSORT guidelines for evaluation of randomised controlled trials (Schulz et al. 2010) and conform the CONSORT extension for non-pharmacological treatment interventions (Boutron et al. 2008).

### Trial design

The SWORD-study is a longitudinal, multicentre, two-arm, randomised controlled trial with one intervention condition (CBT) and one control condition; treatment as usual (TAU). Four assessments will take place for both trial conditions: baseline (T0, before randomisation), 3 (T1), 9 (T2) and 15 months (T3) after the baseline assessment. For survivors in the intervention condition, the CBT will take place between the first and second assessment. The longitudinal design allows for the assessment of both short-term and long-term effects of the intervention.

### Ethical consideration

The SWORD-study has been approved by the ethical review board of the Radboud University Medical Center (CMO Arnhem-Nijmegen). Approval of local ethics has been obtained in centres where recruitment will take place. Only survivors who have completed written informed consent will be allowed to participate. The study will be conducted in compliance with the guidelines for Good Clinical Practice and the Declaration of Helsinki (Pieterse 2010; World Medical Association & Declaration of Helsinki 2013). This trial is registered in the Netherlands National Trial Register (trial number NTR4423).

### Participants and procedure

A total of 104 (breast, prostate or colorectal) cancer survivors with high FCR are to be enrolled in this study. They will be randomly allocated to receive either CBT (n = 52, intervention condition) or TAU (n = 52, control condition). Cancer survivors will be recruited from outpatient clinics at an academic centre and several general hospitals in the Netherlands. Recruitment will take place at all sites simultaneously until the desired sample size is reached. Nurse practitioners are asked to provide an envelope containing study information (and an entry form) to all cancer survivors who are eligible for study participation based on information from their medical record. If interested to participate, a person will complete the entry form at home and send it to the researcher [name] who will then contact them by phone to provide further study information and to address questions. Those willing to participate are asked to provide written informed consent and to fill-out a screening questionnaire. After receipt of the completed questionnaire, the researcher will contact the patient once more to discuss the screening outcome and to second check all eligibility criteria.

### Eligibility

Cancer survivors will be eligible to participate if they: (1) have completed primary treatment (with curative intent) for breast, colorectal or prostate cancer at least 6 months and not more than 5 years ago; (2) are disease-free at the moment of study inclusion, as defined by the absence of somatic disease activity parameters; (3) are at least 18 years of age; (4) score ≥ 14 on the Cancer Worry Scale, indicating high FCR; (5) have sufficient Dutch language skills to fill out questionnaires, to understand written text and to engage in active conversation; (6) are able to travel to the Radboud University Medical Center (RUMC) for CBT; (7) have given written informed consent. Cancer survivors are not eligible to participate if they 1) already receive psychological/psychiatric treatment at moment of inclusion; or 2) have a second primary tumour at moment of inclusion.

### Sample size

The sample size is calculated for the primary outcome FCR as measured with the Cancer Worry Scale (Custers et al. 2014). To detect a medium difference in FCR (Cohen’s d = 0.50), with a two-sided type I error rate of 0.05 and a power of .80, a sample size of 128 patients is needed. To correct for the baseline measurement as covariate the sample size is multiplied with the factor (1-r^2^), where r denotes the correlation between the baseline and post-intervention FCR (0.6 based on preliminary research) (Heinrichs et al. 2012). Therefore, a total sample size of 82 patients is desired. Because of an anticipated attrition rate of 20%, 52 patients are required per condition (104 total) (Lebel et al. 2014).

### Randomisation

After completion of baseline assessment survivors will be allocated to CBT or TAU according to a computer generated randomisation list, with a 1:1 allocation ratio using a fixed block size of six participants. Stratification by cancer type (breast, colorectal and prostate cancer) will be applied Randomisation is computerised, using a randomisation website specifically designed for this study. An independent secretary will enter all necessary patient data into the programme and will communicate the randomisation outcome (CBT or TAU) to the researcher who further informs the study participant. Cancer survivors allocated to the CBT condition will be assigned to one of two therapists according to therapist availability.

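### A fixed block of six per cancer type could let the researcher, who is told every allocation and appears to make the final eligibility check, deduce up to about a quarter of assignments

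*Protocol article*

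**What the plan says.** All sources are sections of the Protocol article.

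- **Scheme.** Under Randomisation, allocation is "with a 1:1 allocation ratio using a fixed block size of six participants". "Stratification by cancer type (breast, colorectal and prostate cancer) will be applied". Centre is not named as a stratum, so there are three sequences in all.
- **Timing.** "After completion of baseline assessment survivors will be allocated to CBT or TAU according to a computer generated randomisation list".
- **Who learns the result.** An independent secretary enters the data in the randomisation website and "will communicate the randomisation outcome (CBT or TAU) to the researcher who further informs the study participant".
- **Who confirms eligibility.** Under Participants and procedure, after consent and the screening questionnaire, "the researcher will contact the patient once more to discuss the screening outcome and to second check all eligibility criteria".
- **Size.** "A total of 104 (breast, prostate or colorectal) cancer survivors with high FCR are to be enrolled in this study".

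The article describes no variation in block size and no step that keeps the block size or the running allocations from the researcher.

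**The concern.** The secretary and the website hide the list. They do not hide what can be worked out from past results. The comparison is CBT against usual care, the researcher hears each outcome, and the cancer type of the next candidate is known beforehand. Once three places in one arm of a block are used, every remaining place in that block must go to the other arm.

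What is at stake is selection before allocation. The person making the last call can influence timing and encouragement, and has some judgement over criteria such as language skills and ability to travel for therapy (Eligibility). Interest in therapy varies: in the needs assessment (Developmental process), 30% of breast cancer survivors with high FCR said yes to CBT and 35% said possibly. If keener candidates were steered towards expected CBT places, the arms could differ in motivation. The primary outcome, the Cancer Worry Scale (CWS), is self-reported, and Table 2 lists no measure of motivation for therapy.

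**Working it through.** **Plan's own figure.** The article gives none for predictability. Its total of 104 does reproduce. For d = 0.50, two-sided alpha 0.05 and power 0.80, the t-test needs 64 per arm, so 128. Then 128 × (1 − 0.6²) = 81.92, rounded to 82, or 41 per arm. Finally 41 / 0.80 = 51.25, rounded to 52 per arm, so 104.

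**Inputs.** Block of 6 with 3 CBT and 3 TAU; three strata; 104 participants; every past allocation known to the researcher (Randomisation; Participants and procedure). Assumption: the researcher knows the block size.

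**Certainty in one complete block.** There are 6!/(3!·3!) = 20 equally likely orders. A place is certain when one arm already has its three.

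- Places 1 to 3: probability 0.
- Place 4: the first three must be alike, 2/20 = 0.10.
- Place 5: the last two must be alike, 8/20 = 0.40.
- Place 6: always, 1.00.

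The sum is 1.5 of 6, or 25%. The closed form for a block of 2m agrees: 2m/(m + 1) = 6/4 = 1.5.

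**Best guess.** Choosing the arm with more places left is right with probability 0.5, 0.6, 0.6, 0.7, 0.7 and 1.0 at places 1 to 6. The sum is 4.1 of 6, or 68.3%, against 50% by chance.

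**Incomplete last blocks.** 104 is not a multiple of 6, so the 25% cannot be applied to the whole total. The stratum sizes are not given, so all splits were examined.

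- Lowest, for example 35/35/34: (5 × 1.5 + 0.5) + (5 × 1.5 + 0.5) + (5 × 1.5 + 0.1) = 23.6, and 23.6/104 = 22.7%.
- Highest, for example 60/24/20: 15 + 6 + 4.5 = 25.5, and 25.5/104 = 24.5%.

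**Candidates still waiting.** The eligibility check comes before baseline and allocation. Each earlier candidate of the same cancer type who is checked but not yet allocated removes one known result. For complete blocks:

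| Same-type candidates waiting | Certain at the check | Best guess right |
|---|---|---|
| 0 | 25.0% | 68.3% |
| 1 | (0.10 + 0.40)/6 = 8.3% | 60.0% |
| 2 | 0.10/6 = 1.7% | 56.7% |
| 3 | 0% | 53.3% |

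**Varied blocks, for comparison.** This is an illustrative simulation: one sequence of 104, and a guesser who knows the set of sizes but not their order. Randomly mixed blocks of 4 and 6 leave about 5.5% of assignments certain, and blocks of 4, 6 and 8 about 2.2%. Fixed sixes on the same footing leave 24.5%.

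**The case against.** The strongest reply is that the article separates the tasks sensibly, so the room for selection is small. Nurse practitioners, who are not said to hear allocations, hand study information to all record-eligible survivors. Consent and the screening score precede the researcher's final call. Most criteria are objective: the CWS threshold, time since treatment, age, no current psychological treatment, no second primary tumour. All sites recruit at the same time and the baseline questionnaire set is long, so candidates of the same cancer type may well be waiting. All of this stands, and it lowers the risk. It does not remove it, because timing, encouragement and the softer criteria remain, and a small stratum may often have nobody waiting.

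A reader might infer more than the article supports:

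- **That a quarter of assignments, 26 of 104, are known in advance.** This applies the complete-block rate to an incomplete total and assumes an empty queue every time. The article gives neither accrual rate nor baseline turnaround.
- **That allocations were predicted or manipulated.** Nothing shows this. The article does not say outright that the same person fills both roles, or that this person knows the block size. The first rests on the shared title and the second on the article itself printing the size.
- **That any resulting bias is beyond repair.** Baseline CWS is measured before allocation and the sample size section treats it as a covariate, so selection acting through baseline fear is adjusted for. What remains is selection on unmeasured features such as motivation.

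**Conclusion.** The point holds as a conditional weakness of the design. A fixed block of six in three strata, with every result told to a researcher who appears also to make the final eligibility check, allows at most 22.7% to 24.5% of assignments (about 24 to 25 of 104) to be deduced with certainty, and best guesses to be right at most 68% of the time. At the eligibility check, the certain share can lie anywhere from zero to that maximum, depending on how many candidates of the same cancer type are waiting.

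This rests on three assumptions: one role does both tasks, that role knows the block size, and it keeps a tally per cancer type. The finding concerns opportunity only. It is worth acting on because the remedy is cheap, and because the baseline covariate would not adjust for selection on motivation.

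**What to change.** For all blocks not yet opened, use randomly varying block sizes, for example 4, 6 and 8, within each cancer-type stratum. Withhold both the sizes and their order from the researcher. Blocks already opened stay as they are.

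This mainly removes certainty. Some advantage over 50% in guessing would remain, and its size under mixed blocks was not calculated.

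The cost is a small change to the randomisation list or website, and a slightly larger possible imbalance at the end of the trial: an unfinished block of eight can leave the arms of a stratum apart by 4, against 3 for a block of six. Requiring eligibility to be logged as final before the allocation request would add little, because the article already puts the eligibility check before baseline and allocation, and such a log would not remove foreknowledge.

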## Intervention

### Developmental process

The development of the intervention consisted of five stages:

● *Needs assessment:* Breast cancer survivors (n = 130) were approached with a ‘need for help’ question and the Cancer Worry Scale (CWS) (Custers et al. 2014). All survivors were asked if they would accept CBT specifically focused on managing FCR when experiencing high FCR (response options: yes/possibly/no). They were also provided with a short explanation of the CBT-content and therapy outline. Eighty-seven survivors completed both the ‘need for help’ question and the CWS. The majority (74%) of the responders considered or expressed a need for CBT (44% possibly; 30% yes). Almost the same response pattern was seen in those with high FCR (35% possibly; 30% yes) and those with low FCR (50% possibly; 30% yes) as based on the CWS. This procedure was replicated amongst 86 colorectal cancer survivors. Fifty-six percent of these survivors considered or expressed a need for CBT (38% possibly; 18% yes). Colorectal cancer survivors with high FCR were more open to CBT compared to survivors with low FCR (Low FCR, 38% possibly; 10% yes: High FCR, 39% possibly, 32% yes). Thus, a substantial number of cancer survivors indicate a need for help with FCR.

● *Content and structure of the intervention.* The intervention was developed by a collaboration of three clinical psychologists [name], two researchers [name] and a psychiatrist [name], all experienced in the field of psychosocial oncology and working at the RUMC. After literature consultation and multiple meetings, consensus was reached on core components and key techniques of the intervention (described in the section ‘Intervention: Cognitive Behaviour Therapy for FCR’).

CBT is one of the best established interventions for psychological problems in somatic conditions. In health care settings, CBT is already frequently used for various somatic problems such as fatigue and insomnia (Savard et al. 2005; Gielissen et al. 2006). CBT is a structured, action-oriented form of psychological treatment consisting of techniques directed at identifying and modifying negative (dysfunctional or unhelpful) thought patterns and dysfunctional behaviours (Beck & Beck 2011). Since cognitions, emotions and behaviours are interconnected, a change in cognitions and/or behaviour initiates changes in the other areas as well.

The intervention will be offered as blended therapy. In blended therapy both online and offline therapy components are integrated. A website is available that supports the patient throughout the entire therapy as it runs parallel to the face-to-face therapy sessions. The website has been developed in collaboration with ICT specialists and contains over 70 pages of content including information (10 scripts), at-home assignments (27 tasks), assessments (6 tests), audio (2 clips) and video (15 fragments). An incorporated library includes additional information on cancer-related topics. A feature to engage in an electronic consultation (‘e-consult’) with the assigned therapist is supplementary to the face-to-face sessions. Because not all survivors have access to the internet and some may lack the required computer skills, a paper workbook (with DVD/CD) will be available as well.

● *Advisory Committee.* The third step was to involve health care workers and patient representatives as an advisory committee in reviewing the therapy content. The committee was composed of three cancer survivors (breast, colorectal and prostate cancer) and three health care workers (two nurse practitioners for breast cancer and colorectal cancer care and a urologist). They were asked to provide comments, ideas and suggestions to further improve the intervention. In addition, a 13-item close-ended questionnaire, answerable on a 5-point Likert Scale (e.g. “*Overall, what is your general impression of the website?”*) was completed and members were asked to elaborate on their assigned score. The content and format of the intervention were rated with a mean of 4.3 out 5 (a higher score indicating a more positive impression of the intervention). With the generated feedback the content was slightly revised.

● *Website usability testing*. The user interface of the prototype website was tested by three patient representatives (breast, colorectal and prostate cancer) on feasibility and patient centeredness. A ‘think aloud procedure’ was employed, meaning that persons were asked to think aloud while using the website in order to provide us with more insight in 1) how the website is used without guidance of a professional and 2) how encountered problems are solved (Jaspers 2009). Afterwards the System Usability Scale (SUS) (Brooke 1996; Bangora et al. 2008) and a feedback form were completed. The SUS is a short (10-item scale) which gives a global view of subjective perception of usability, the mean total SUS score (range 0 - 100) given by the three survivors was 87, which indicates a satisfactory level of perceived usability (Bangora et al. 2008).

● *Pilot testing.* Lastly, two therapists piloted the intervention with two high fearful breast cancer survivors who completed all therapy sessions. After some minor revisions, the final content of the therapy manual was established.

